## Abstract

**Background:**

In the eastern part of the Democratic Republic of Congo (DRC) Village Savings and Loan Associations (VSLAs) programs targeting women are implemented. In the context of the ‘Mawe Tatu’ program more equitable intra-household decision-making is stipulated by accompanying women’s participation in VSLAs with efforts to engage men for more gender equality, expecting a positive effect of this combined intervention on the household economy, on child nutritional status, on the use of reproductive health services including family planning, and on reducing sexual and gender-based violence (SGBV).

**Methods:**

A longitudinal parallel mixed method study is conducted among women participating in VSLAs in randomly selected project areas and among a control group matched for socioeconomic characteristics. Descriptive statistics will be calculated and differences between intervention and control groups will be assessed by Chi2 tests for different degrees of freedom for categorical data or by t-tests for continuous data. Structural equation modelling (SEM) will be conducted to investigate the complex and multidimensional pathways that will affect household economic status, child nutritional status and use of reproductive health services. Analysis will be conducted with STATA V.15.

Concomitantly, qualitative data collection will shed light on the intra-household processes related to gender power-relations that may be linked to women’s participation in economic activities and may lead to improvements of maternal and child health. Focus group discussions and in-depth interviews will be conducted. All narrative data will be coded (open coding) with the help of qualitative data analysis software (Atlas TI).

**Discussion:**

Women’s empowerment has long been identified as being able to bring about progress in various areas, including health. It has been shown that men’s commitment to transforming gender norms is a sinequanone factor for greater equity and better health, especially in terms of reproductive health and child nutrition. This study is one of the first in this genre in DRC and results will serve as a guide for policies aimed at improving the involvement of men in changing attitudes towards gender norms for higher household productivity and better health.

## Background

Maternal and child health are among the most important indicators of a country’s development. Major causes of maternal mortality can be prevented and treated with simple, affordable health interventions such as antenatal care (ANC) or vaccination if used adequately and on time [1]. Children’s nutritional status is a sensitive indicator for household poverty, with childhood malnutrition having many long-term effects for health [2–4]. The Democratic Republic of the Congo (DRC) is among the poorest countries in the world and heavily indebted with high rates of maternal and child mortality [5]. The country was ranked as the 176th of 188 countries in terms of human development index [5]. In 2015 maternal mortality was estimated at 693 per 100,000 and the under-five mortality rate was around 308 per 1000 [6]. Malnutrition is rampant where 43% of children under five are malnourished and around 76% of women encounter barriers accessing maternal health care services [7]. The country has been involved in repetitive wars for over 20 years, and the East of the country is still facing rebellions. Insecurity prevails and unemployment is widespread. Like in many other countries, women ensure much of the economic activities of a household, and largely carry the responsibility for providing and caring for household members; men endorse the role of decision-making for all expenditures including health [8–10]. This is confirmed according to the Demographic and Health Survey 2014/15, where only 29% women decided themselves how to use the money they have earned. When it comes to decision making about their own health only 36% of the women decided themselves [7]. As women are usually the main caregivers of children, women’s limited decision-making negatively affects their children’s health and wellbeing [11–14]. Men’s involvement remains important though. A lack of participation of men in programs improving sexual and reproductive health has also been revealed as one of the reasons for poor progress observed in the domain of family planning and persisting disagreement between spouses regarding their choice for sexual and reproductive health service use [15–18]. Studies showed that male involvement led to better results regarding the use of contraceptives [18–20]. Barker and others have further demonstrated that the involvement of men in family health can be a mediator towards better health [21–24].

Women’s empowerment is a process of awareness and capacity building leading to greater participation, to greater decision-making power, and to transformative action in different domains such as rights, health, or economics [8, 25]. In the literature, economic empowerment was presented as a key factor for better health and to palliate all types of violence including intimate partner violence [26–28]. However, in a male-dominated society, women’s economic empowerment is not the sole factor to fight partner violence and can lead to resistance due to restrictive gender norms. Therefore, actions engaging men to support women’s empowerment must be part of interventions that aim at strengthening women’s economic participation [29–31] .

It has been shown that sufficient resources and an enabling environment allows women to make decisions about their own health, which leads to improved health outcomes specifically as regards sexual and reproductive health (SRH) [32–35]. Yet, in South Kivu and in other African contexts women often lack access to health services and also the financial resources to meet every day needs [9, 36]. As both are required, improvement of cash income, and a more equitable decision-making about the use of resources at the level of the household, complex interventions combining those two aspects are needed.

One of the most widely implemented approaches to improve population health is the introduction of microfinance including projects containing a social development component such as Village Savings and Loans Associations (VSLA) [37–40]. A VSLA is a platform for developing women’s capacities in organizational and financial matters, to improve self-efficacy and decision-making, and other skills. This approach was receiving increasing attention in the 1990s as a community-managed microfinance approach with a social mobilization component [41]. A VSLA is a self-selected group of 25 to 30 persons who agree to save a certain amount defined by all the members every week. Members self-organize in a committee with a president and meet every week. Loans can be taken up to 3 times the savings a member has contributed, and the loan has to be paid back with an interest rate of 5–10% according to what the group has defined. A normal cycle of a VSLA is nine to 12 months, after that a new VSLA has to be set up.

Several studies evaluated VSLA programs showing positive effects on general welfare and on child well-being [37, 39, 42]. Positive impacts on health were stronger if VSLA programs were in conjuncture with health education [21, 35, 43]. There is some evidence on the effectiveness of VSLAs in fragile contexts, which focused on specific subgroups. A study in post-conflict Ivory Coast showed positive effects of an intervention focusing on gender relations in combination with VSLAs on household economies and gender equity [29]. In Eastern DRC, a project evaluation among female sexual violence survivors showed a positive effect of a VSLA program on food consumption and stigma reduction [44]. A limitation of the approach is however the self-selection process when forming VSLA groups, which can lead to the exclusion of socially marginalized persons if they are not explicitly targeted [41, 45].

To improve gender equity within households, several approaches towards engaging men for gender equity have been developed, a prominent example being the Promundo approach, which is based on men-to-men sensitization developing ‘positive masculinity’. Men engage men towards more equitable gender norms to adopt attitudes and behaviour promoting women’s economic empowerment and helping to reduce gender based violence; “Positive masculinity” refers to positive changes in attitudes and behaviours transforming the socio-cultural norms associated with masculinity [46, 47]. Once men are sensitized to the benefits of women’s empowerment, they could become active advocates for women’s and children’s welfare in the household as well as in the community and change gender-based inequities in health [38].

Increasingly, projects target women and men jointly in order to transform gender-inequitable norms and behaviors, yielding encouraging results for example on reducing gender based violence [30, 48, 49]. Projects engaging men can be part of complex interventions, but only a few have combined these approaches with VSLAs [29, 31].

### Mawe tatu program

The “Mawe tatu” program, implemented in the Eastern part of the Democratic Republic of Congo, links VSLAs for women with men-to-men sensitization to transform gender-inequitable norms and behaviors, and additionally combines these two project arms with an educational component about family planning and sexual and reproductive health. The project is implemented by CARE international, with the three components linked to three main objectives:
empowerment of women by organizing them in Village Savings and Loans Associations (VSLA). An important component of a VSLA besides the financial aspect is the development of women’s capacities in organizational and financial matters, to improve self-efficacy and decision-making, and other skills. In addition, different discussion topics are developed during the cursus to further improve knowledge and skills: Human Right, Leadership, Governance, House Economics, Conflict Resolution, Family Planning, Gender Equity and Diversity.Developing ‘positive masculinity’ by engaging men, if possible spouses of VSLA’s members, towards women’s rights using a peer-to-peer approach. Men should sensitize each other and organize themselves in reflection groups in order to adopt attitudes and behaviours promoting women’s economic empowerment and reducing gender based violence. Sensitisation includes the following themes: identity and the concepts of gender; masculinities; the cycle of male and female socialization; the socialization of gender: acting as a man, acting like a woman; men and interpersonal violence; gender-based violence (GBV); involvement of men in the prevention of GBV; the ten tips for a good fatherhood: sharing of work and child care within the household; fair negotiation, equity and equality; economic partnership; mutual respect and dialogue between spouses; family planning; dissemination methodology.As a third component comprehensive sexuality education for young people, which includes gender and rights themes, is offered as well. The three approaches work in interaction sustaining women’s empowerment in order to increase gender equity, reduce poverty and improve health at the level of households and at the level of community (Fig. 1). The evaluation of the third component is not part of this protocol.

**Fig. 1 Fig1:**
[figure not shown]
Mawe tatu’s Project framework

This research aims to clarify (a) the impact of a complex intervention associating VSLA program with men’s engage program on reproductive and child health indicators, and (b) to clarify the contribution of a peer-to-peer sensitization approach engaging men for more equitable gender norms as part of a complex intervention. Main outcomes include household economy, gender norms and gender-based violence, and women’s confidence to participate in household- and community-decision-making processes. Reproductive and child health outcomes include child nutritional status, utilization of antenatal care services, facility-based delivery, family-planning counselling, and women’s self-rated health (Fig. 1).

### Conceptual framework

A framework has been developed to operationalize how “positive masculinity” in combination with women’s economic empowerment impact on the economic status of the household and on health and wellbeing (Fig. 2).

**Fig. 2 Fig2:**
[figure not shown]
Research framework

Through the MaweTatu project, men are sensitized for women’s rights, including sexual and reproductive health rights. Together with women participating in VSLAs they are expected to become agents of change as regards the transformation of gender norms, which will lead to more gender-equitable attitudes, joint intra-household decision-making, and increased economic activities and autonomy among women. It is further expected that engaging men for gender equity enhances health and wellbeing of the family, including children’s nutritional status.

## Methods

This research will employ a parallel mixed-method design, combining a longitudinal cohort study (Study1) with a longitudinally designed qualitative study (Study 2). Quantitative findings will be triangulated with qualitative findings in order to deepen the understanding of the forces that trigger and sustain the expected change.

### Study component 1 - quantitative

#### Study design and study population

A cluster-randomized, longitudinal intervention study compares VSLA participants in an intervention area with controls over a period of 12 months. The intervention districts are identified a priori by the implementing organization, but the intervention and control sites (villages) are randomly selected within these districts. In the intervention sites, all persons participating in a newly created VSLA are eligible for inclusion in the intervention arm. While participation in a VSLA is based on self-selection, a random sample of VSLA participants is selected based on VSLA members’ lists available from the Mawe Tatu project.

A control group of participants is recruited in adjacent randomly selected villages where VSLAs are not offered. Participants self-select to take part in an information session on income-generation or a related theme in order to recruit participants with a similar socio-economic profile as the VSLA members. A random sample of participants of the information sessions is then included in the study as controls. In both the intervention and control areas, a community leader conveys the information about the upcoming activities in a similar way in order to attract a similar group of participants.

Additional inclusion criteria for the study included being long-term residents of the study site (living in the household for at least 6 months) and being at least 15 years old. For participants with children, all children aged 1–5 years currently living in the household of an adult study participant are recruited for inclusion in the anthropometric study module. Children included in the study must be under guardianship of the adult study participant (Table 1).

**Table 1 Tab1:** Study population by intervention and control group, quantitative study component

Study participants	Intervention group	Control group
Women	VSLA member	Participated in information session, not member of a VSLA
Children (1–5 years)	Children who are in guardianship of an adult study participant member of VSLA	Children in guardianship of an adult participating in control group

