#### Sample size calculation/justification

The power calculation is based on the hypothesis that establishing savings and loan systems at the village level lowers the risk of stunting of children up to the follow-up. Improved child growth is a result of increased livelihood and food security that is sustainable over some time. The surveys are conducted in 80 villages with an average of 15 households per village (1200 households). Assuming an attrition rate of 30% during follow-up this results in a final analytic sample size of 800. The control group is planned to be smaller with 40 villages (600 households). Assuming the same attrition rate there must be 400 households recruited to participate in the final control arm.

As there are few data on the distribution of individual growth rates among children in the study area, we express the intervention effect in terms of a certain fraction of the standard deviation SD of individual growth rates. If the mean change in height during a given time period increases by z standard deviations as a consequence of the intervention, then this corresponds to a shift of the median of growth to the Φ (z)-quantile of the distribution in the control group (where Φ denotes the cumulative density function of the standard normal distribution. For instance, if z = 0.25, this corresponds to an intervention-related shift of the distribution whose new median is where the 60th percentile of the original distribution was.

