First, descriptive statistics will be calculated for the primary and secondary outcome variables, and for socio-economic characteristics. Assets, number of income-generating strategies, food security and child nutritional status, use of family planning and other reproductive health services, and related knowledge, and prevalence of perceptions of gender relations (beliefs and attitudes), and prevalence of different levels of knowledge on sexual and reproductive health including use of family planning methods and existing services will be documented. For this purpose, percentages, means and standard deviations will be computed. To assess self-efficacy and decision-making power, indices will be built using Mokken analysis, which is a nonparametric procedure based on item-response theory that has been used to assess similar scales in previous studies [55, 56]. Differences between education level, rural and urban populations will be assessed statistically using Chi2 tests for different degrees of freedom for categorical variables, or using t-tests for continuous variables.

To assess the program effects, mixed-effect regression models will be run for each primary outcome variable to establish change in the outcome variables over time (baseline to endline) and by intervention and control group. The models will be adjusted for socio-economic confounders, and clustering will be considered at the level of villages. The same analysis as for primary outcomes will be conducted for secondary outcomes. In addition, the role of mediating factors will be investigated. It will be explored whether a change in the power of decision-making mediates changes in household economic status and use of family planning (FP). In addition, we will study whether children’s nutritional status improves if men are supportive of women’s economic activities. For this purpose structural equation modelling (SEM) with maximum likelihood estimation will be conducted to investigate the complex and multidimensional pathways by which the association of a positive masculinity and women’s empowerment directly or indirectly affect household economics status, children nutritional’s status and use of reproductive health services, and the potential role of mediating variables.

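### Villages are selected within districts, but the effect models name no district term; adding one is a nearly free gain in precision

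*Protocol article*

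**What the plan says.** **Design (Protocol article, Study design and study population).** The districts are not random: "The intervention districts are identified a priori by the implementing organization". Within them, "the intervention and control sites (villages) are randomly selected within these districts". For the comparison arm, "A control group of participants is recruited in adjacent randomly selected villages where VSLAs are not offered".

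**Size (Sample size calculation/justification).** The intervention arm has 80 villages and the control arm 40, with about 15 households in each. After attrition, 800 and 400 households are expected in the analysis. No breakdown by district is given.

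**Analysis (Statistical analysis plan, program-effects paragraph under Secondary outcomes).** Mixed-effect regression is to be run for each primary outcome "to establish change in the outcome variables over time (baseline to endline) and by intervention and control group". The structure given is: "The models will be adjusted for socio-economic confounders, and clustering will be considered at the level of villages". Secondary outcomes get the same analysis.

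**Elsewhere.** Table 2 lists no district or area variable. The only cluster component in Table 3 is the village, with ICCs of 0.01 to 0.05 cited from other African settings and 0.10 also tabulated.

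**The concern.** A design that draws both arms within the same districts can remove district differences from the arm comparison. That benefit reaches the standard error only if the analysis uses the same grouping. The models as described go down to the village and leave out the level above it, within which the villages were selected.

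Two things could be at stake. The first is precision: if districts differ in how outcomes change over the 12 months, and each district has the same arm ratio, that variation is balanced between arms in fact but still counted as village noise. The second is conditional: if the arm ratio is not the same in every district, district differences in change could enter the estimated arm effect.

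**Working it through.** **1. Inputs.** From the article: 80 and 40 villages; 800/80 = 400/40 = 10 analysed households per village; effects of 0.2 and 0.25 SD; village ICC 0.01 to 0.05. (A 30% loss from 1200 and 600 would leave 840 and 420; Table 3 fits the smaller figures.) Not in the article and therefore assumed: two-sided alpha 0.05, the number of districts, and the share f of village variance lying between districts, taken as 25-50%.

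**2. Reproducing Table 3.** With the SD read as the within-village SD and m children per village:

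SE² = [ICC/(1 − ICC) + 1/m] × (1/80 + 1/40), power = Φ(d/SE − 1.96).

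At ICC 0.05 and m = 10: SE² = (0.0526 + 0.1) × 0.0375 = 0.00572, so SE = 0.0757.

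- d = 0.2: Φ(2.644 − 1.96) = 75.3% (Table 3: 75%).
- d = 0.25: Φ(3.304 − 1.96) = 91.1% (Table 3: 91%).

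With m = 10 or 5, all 27 power entries in Table 3 reproduce within 0.5 points.

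**3. Adding district, with 2:1 in every district.** A district term removes the share f from the village component:

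SE² = [(1 − f) × ICC/(1 − ICC) + 1/m] × 0.0375.

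At ICC 0.05, SE falls to 0.0723 (f = 25%) or 0.0688 (f = 50%). Without the term the reported SE is too wide by a factor of 0.0757/0.0723 = 1.046 or 0.0757/0.0688 = 1.099.

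| Effect | ICC | Table 3 formula | District term, f = 25% | District term, f = 50% |
|---|---|---|---|---|
| 0.2 SD | 0.05 | 75.3% | 79.0% | 82.8% |
| 0.25 SD | 0.05 | 91.1% | 93.3% | 95.3% |
| 0.2 SD | 0.01 | 87.5% | 88.3% | 89.0% |
| 0.25 SD | 0.01 | 97.3% | 97.6% | 97.8% |

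The first power column is the planning figure, which counts all village variance as noise. With a constant ratio, the estimate itself varies less than its reported SE suggests, so a test without the term does slightly better than that column: power = Φ((d − 1.96 × SE without term)/SE with term). At 0.2 SD and ICC 0.05 this gives 76.3% (f = 25%) or 77.4% (f = 50%). The gain over the analysis as described is then about 3 to 5 points, against 4 to 8 over the planning figure.

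**4. Validity of the test.** Village-level simulation with no effect, 4 or 8 districts and f = 50%:

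- *2:1 in every district, no term:* mean estimate about 0; type I error 3.6-3.9% at ICC 0.05 and 2.3-3.2% at ICC 0.10. With the term, 4.7-5.5%.
- *Random allocation ignoring district, no term:* mean estimate about 0; type I error 5.1-6.0%; SD of the estimate 0.074-0.088, against 0.071-0.079 with the term.

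**5. When bias would arise.** With two districts, bias = (difference between arms in the share of villages from district A) × (district difference in mean change). For an assumed 0.2 SD difference in change:

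- 50/50 in both arms: 0 × 0.2 = 0.
- 60/40 against 40/60: 0.2 × 0.2 = 0.04 SD.
- 70/30 against 30/70: 0.4 × 0.2 = 0.08 SD.

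If either factor is zero, there is no bias.

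**The case against.** The strongest reply is that this is silence in a condensed article. The covariates are not itemised, so district may appear in a fuller plan, and nothing here excludes it. That stands as a limit on wording: the models name no district term, which is not the same as ruling one out. It does not dispose of the point, because the article does state the type of adjustment and the clustering level, and a geographic selection unit is not naturally read as a socio-economic confounder.

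It can also be said that selection within districts may mean drawing from the pool that the districts form, not district by district. On that reading the analysis without district is valid (step 4, second case). This too stands; the term would still tighten the estimate.

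A reader might infer that leaving out district confounds the comparison, or biases every primary estimate. The article does not support this. Both arms come from the same districts, and control villages are adjacent. The models estimate change, so stable district differences in level, such as baseline nutrition, largely cancel. Bias needs both an arm ratio and a change over time that differ by district. The article neither states nor rules out that combination.

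Finally, the gain is small at the 0.25 SD effect that the sample size section uses as its example: about 0.3 to 4 points over the planning figure across ICC 0.01 to 0.05. That is correct, and it sets the weight of the point.

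**Conclusion.** The point holds as a free improvement, not as an error that invalidates the analysis. The described models do not name the grouping within which villages were selected. With a constant arm ratio the consequence is a conservative test: at ICC 0.05 the reported standard errors are about 5-10% too wide, and a district term takes calculated power from 75% to 79-83% at 0.2 SD and from 91% to 93-95% at 0.25 SD. At ICC 0.01 the gain is negligible.

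These sizes rest on the assumed 25-50% between-district share, alpha 0.05 and a 2:1 ratio in each district. The direction of the precision loss needs only that ratio and some between-district variation in change. No inflated false-positive risk from the omission is shown. Bias remains a conditional possibility that a count of villages by arm and district would settle.

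**What to change.** In the program-effects paragraph of the Statistical analysis plan, state that the mixed models for all primary and secondary outcomes include district as a fixed effect together with its interaction with time, alongside the village clustering already planned. The interaction matters because the effect is read from baseline-to-endline change; a district main effect alone absorbs only differences in level. Also report the number of intervention and control villages in each district, so that readers can see whether 2:1 holds throughout.

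The cost is about one sentence and one small table. District should be known for every village, since villages were drawn within districts, so no new data are needed. The statistical price is a few degrees of freedom out of 120 villages; the exact number depends on how many districts there are, which the article should also state.
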